## Abstract

**Introduction:**

Children with severe eosinophilic asthma are at an increased risk of severe exacerbations, medication side effects, impaired lung function, and significantly reduced quality of life. The advent of biologic agents aimed at eosinophilic pathways has significantly improved management options for patients with severe asthma.

Mepolizumab, an anti-interleukin-5 monoclonal antibody, was approved in 2018 as an add-on maintenance treatment for patients with severe eosinophilic asthma aged ≥6 years of age. Mepolizumab’s efficacy and safety is well documented in adults, but paediatric data remain limited. This real-world observational study will evaluate the long-term safety and efficacy of mepolizumab in children and adolescents, including those with comorbidities and on concomitant medications to provide a clearer picture of its performance in everyday clinical practice.

**Methods and analysis:**

Design: CASAM is an open label, multinational (Spain and United Kingdom), multicenter (15 Spanish and 6 UK public institutions) observational cohort study. Sample size: 150 paediatric patients on mepolizumab for SA between 6–17 years of age will be enrolled. Study Duration: Study will be conducted over 36 months (12 months pre mepolizumab initiation and 24 months after initiation). Data Collection: Pseudonymized data (prospective and retrospective) from medical charts will be collected and entered in the electronic case report forms (eCRFs) of the electronic data capture (EDC) system. Primary Outcome: To compare the rates of clinically significant asthma exacerbations in the pre-exposure and the 12-month post-exposure period with mepolizumab treatment. Protocol Version: CASAM Study_Protocol_V2.0_16th November 2023 KCH

**Registration details::**

The study is registered with ClinicalTrials.gov (NCT05139381), IRAS number 306475.

## 1. Introduction

Around 11% of children aged 6–12 years old worldwide suffer from asthma [1–3], making it the most common chronic illness in paediatrics [4]. Although the majority of children & young people (CYP) with asthma are able to control their symptoms with available standard of care treatment, about 2–5% have severe asthma (SA) and need regular high-dose inhaled corticosteroids (ICS), a second controller, and/or chronic systemic corticosteroids for management [5–7]. A study conducted across 30 paediatric pulmonology and allergy units in Spain reported a SA prevalence of approximately 8.8% to 24.2%. Children with SA face higher risks of severe exacerbations, medication side effects, impaired lung function, worse quality of life (QoL), and increased adult chronic obstructive pulmonary disease (COPD) risk compared with mild/moderate asthma [6–14]. Adolescents with SA have more frequent hospitalizations as compared to the adults with SA [15], significant school absenteeism [16] thus a higher disease burden

Inflammation in severe asthma can be categorised as either eosinophilic or neutrophilic [5]. The eosinophilic phenotype is characterised by airway infiltration with eosinophilic inflammatory cells leading to poor asthma control, frequent exacerbations, greater risk of near-fatal asthma attacks and reduced lung function. This poses a huge burden on caregivers, increased healthcare utilisation and cost, reduce quality of life (QoL) [9,13,17]. Therefore, there remains a need for safe and effective treatment options that target diverse inflammatory pathways. Deeper understanding of asthma endotypes and phenotypes led to development of monoclonal antibodies (mAb) (Biologics) that target specific inflammatory pathways.

Mepolizumab got approved as an add on therapy for the treatment of eosinophilic SA in children ≥6 year of age in Europe in 2018. It is a humanised, anti-IL5 antibody (immunoglobulin G (IgG) Kappa) that binds with high affinity to human IL-5, thus regulates activation of the IL-5 receptor present on eosinophils and basophils [1,18]. In Phase 3 adult trials, adding subcutaneous (SC) mepolizumab to standard care significantly reduced exacerbations, decreased maintenance corticosteroid dependency, improved symptom control and health related QoL [19–25].

### Mepolizumab in 12–17 years

In Phase II and III clinical trials, due to the low prevalence of severe eosinophilic asthma in adolescents, recruitment was challenging. A total of 37 adolescent patients were randomized across the 4 mepolizumab trials [26]: the 32-week MENSA study [22] (n = 25; NCT01691521); 24-week MUSCA study (n = 9; NCT02281318) [20]; 52-week DREAM study (n = 1; NCT01000506) [27]; and 24-week SIRIUS study (n = 2; NCT01691508) [19]. Of the 37 recruited patients from MENSA and SIRIUS study, 26 entered COSMOS (NCT01842607) [21], a 52-week, open-label extension study to understand long term safety of mepolizumab. In this study all patients received 100 mg SC mepolizumab. MUPPITS-2 trial is the largest randomised trial in paediatrics which enrolled 290 children and adolescents aged 6–17 years [28]. In the adolescents, the asthma control trended in favour of mepolizumab with overall significant reduction in exacerbations. The adverse event (AE) reported (headache, nasopharyngitis, and upper abdominal pain) were broadly consistent with the overall population [19–21,23–29] and like adult studies, reduction was noted in blood eosinophil counts [19,20,22,26,27,30].

### Mepolizumab in 6–11 years

*Gupta et al*, in their multi-national, non-randomised, open-label, pharmacokinetic trial reported first clinical evaluation of mepolizumab SC in children aged 6–11 years with severe eosinophilic phenotype [31]. Mepolizumab SC half-life of 22–24 days in children was congruous with adult value of 16–22 days. Mepolizumab was deemed to be safe in children with no specific AE patterns and no new safety concerns beyond those seen previously in adults and adolescents over 52 weeks [19–21,23–25,27,31,32]. They observed sustained reduction in blood eosinophils (to 50 cells/µL) during the 12-week dosing phase in Part A [31], and during the long-term, 52-week dosing phase in Part B [32]. Blood eosinophil reductions correlated with improvements in asthma control, as shown by ACQ-7 and c-ACT scores. *Jackson et al* in their randomised controlled trial demonstrated a 30% reduction of the AER in the mepolizumab group compared to controls (AER ratio 0.73; 0.56–0.96; P = 0.027), which is less than adult studies [28]. Mepolizumab in trials hasn't demonstrated significant change in function [31,32]. Long term safety data in adults are not associated with opportunistic infections or neoplasms [23]. There is no long term (>52 weeks) safety data or real-world evidence of use of mepolizumab in children & adolescents with SA.

## 2. Rationale

SA in children and adolescents remains a challenging condition to manage. While mepolizumab, has demonstrated efficacy and safety in adult population, paediatric data are limited. Most existing paediatric studies have focused on pharmacokinetics and safety, with few addressing clinical outcomes, and many lacking a comparator arm [28,31]. Recruitment challenges and ethical concerns have also limited the feasibility of trials in this age group. The clinical effectiveness of mepolizumab in children and adolescents, particularly in routine care settings, remains underexplored.

This ‘real-world’ observational study in children and adolescents aims to bridge this gap and assess mepolizumab’s effectiveness and safety in a more diverse paediatric population, with various co-morbidities and concomitant medications. The study will help us understand how the medication performs in real-world clinical practice compared with clinical trials.

## 3. Research question and objectives(s)

To assess the long-term benefit of mepolizumab based on the reduction of clinically significant exacerbations and side effects after long term use.

### 3.1 Primary objective

To compare the rates of clinically significant asthma exacerbations (defined as systemic OCS use and/or ED visit and/or hospitalisation) in the pre-exposure and the 12-months post-exposure period with mepolizumab treatment.

### 3.2 Secondary objective

Compare the rate of mild and moderate clinically significant exacerbations in the pre-exposure and the 12-month and 24-month post-exposure periods with mepolizumab.Compare the rate of severe asthma exacerbations requiring an ED visit in the pre-exposure and the 12-month and 24-month post-exposure periods with mepolizumab.Compare the rate of severe asthma exacerbations requiring hospitalization in the pre-exposure and the 12-month and 24-month post-exposure periods with mepolizumab.Describe changes from index date (date of mepolizumab start) in OCS dose during the post-exposure period among participants on maintenance OCS.Describe asthma related healthcare resource utilization including count of hospital admissions, ED visits, visits to HCPs, and prescription medication utilisation for asthma.Compare prescription medication utilisation (pick up) of ICS & rescue medications in the pre-exposure and the 12-month post-exposure period with mepolizumab treatment.Compare the level of asthma control at baseline and the 12- and 24-month post-exposure periods.Determine and compare the level of asthma severity measured by composite asthma severity index (CASI) score at baseline and the 12- and 24-month post-exposure periods.Determine patterns of mepolizumab usage including adherence/persistence, duration of therapy, discontinuation, and reasons for discontinuation.Determine incidence of Mepolizumab-related adverse events – parents/ patients/ physicians reported.Describe the sociodemographic, socioeconomic, and clinical characteristics (including comorbidities) of the patients under mepolizumab treatment.Describe the Health-Related Quality of Life (HRQL) of patients treated with mepolizumab at the pre-exposure and post-exposure periods.

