### 4.1 Inclusion criteria

A patient will be eligible if all the following criteria apply:

Parents/guardians and/or children & adolescents aged 6–17 years at mepolizumab initiation who provides his/her written informed consent to participate prior to commencing any study related activities.Patient with a current clinical diagnosis of severe asthma (as per GINA/ ATS/ ERS/ BTS criteria) and eosinophilic phenotype (as per mepolizumab licence)Patient currently under treatment or who initiates treatment with mepolizumab at the inclusion visit based on national asthma guidelines.Patient with relevant paper or electronic-based medical records available for 12-months prior to enrolment date/index date (date of first mepolizumab injection).

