**2. Clinical characteristics:**
◦ History of asthma:
▪ Age at asthma onset
▪ Degree of asthma control (c-ACT score at baseline and all follow-up visits)
▪ Degree of asthma severity (CASI score at baseline, 12- and 24 months)
▪ Previous medication for asthma during the 12 months before mepolizumab initiation: type, dose, discontinuation date and reason for discontinuation
◦ Details of current asthma status at baseline and follow-up visits
▪ Lung function data: FEV1 and FVC (if available)
▪ Peripheral blood eosinophils (if available)
▪ FeNO (if available)
◦ History of asthma exacerbations:
▪ Count exacerbations in the year before starting mepolizumab and between follow-up visits.
◦ Co-morbidities at baseline (retrospectively) and at 24 months: atopic dermatitis, allergic rhinitis, obesity, food allergies, GERD, psychological factors, breathing dysfunction (EILO, hyperventilation).
◦ Allergic condition (IgE, skin prick test or Specific IgE to aeroallergens) at baseline.
3. Tobacco smoke exposure at baseline and follow-up visits: Yes (active/ passive)/No.
4. Treatment with mepolizumab at baseline and follow-up visits: type (home/hospital), dose, dose changes, start and end date, discontinuation date and reason for discontinuation.
5. Healthcare utilisation at baseline (during the 12 months before study inclusion) and between follow-up visits.
i. Number of Emergency Department (ED) visits
ii. Number of Unscheduled Outpatient visits
iii. Number of Hospital admissions
6. Satisfaction with treatment with mepolizumab (patients/parents/HCP): VAS 0-5 (very unsatisfied to very satisfied.
7. Adverse Events related to mepolizumab reported by parents/patients/physicians
8. Adapted version of WPAI questionnaire for work productivity and absenteeism (to be completed by parents/legal guardian)
9. Days of school absenteeism (direct question to the parents/tutors)

**Table 2 pone.0335399.t002:** Illustrates overview of patient reported variables collected.

1. c-ACT (Children Asthma Control Test) [33]: It will be completed at baseline and follow-up visits.
2. **Composite asthma severity index (CASI) [****34****]**: It will be completed at baseline and follow-up visits.
3. **Visual Analog Scale (0–5) to measure satisfaction** with treatment for patients, parents, and HCP at baseline (in patients already under treatment) and follow-up visits at 6, 12, 18 and 24 months.

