4. A set of **ad-hoc questions** to collect school absenteeism: absenteeism, late arrivals, or early departures from school in the previous, missed school-related activities, rescue inhaler utilization at school in the previous 12 months before inclusion and every 3 months in the follow-up period.
5. **Work Productivity and Activity Impairment Questionnaire General** (WPAI-GH) [35]: to be completed during the visits by the parents/legal guardians.
6. **Paediatric Asthma Quality of Life Questionnaire** (PAQLQ): It is for children between the ages of 7 and 17 years to be completed during the visits.

**Table 3 pone.0335399.t003:** Illustrates data collection overview.

Activity	Baseline visit Retrospective data (12 months prior mepolizumab initiation and since mepolizumab initiation to inclusion visit in patients already under treatment) and current data	Follow-up visits (according to usual clinical practice, up to 24 visits are expected) *If not available in all FU visits, minimum collected at the selected visits					
		All FU visits	6 m	9 m	12 m	18 m	24 m
**Informed consent**	X						
**Inclusion/exclusion criteria**	X						

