**Demographics/socioeconomic characteristics**							
• Age at mepolizumab initiation • Gender (male/female) • Socioeconomic situation	X						
• Weight • Height • Body Mass Index (auto calculated)	X	X			X*		X*
	**Baseline visit** Retrospective data (12 months prior inclusion) and current data	**All FU visits**	**6 m**	**9 m**	**12 m**	**18 m**	**24 m**

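### For children already on mepolizumab at inclusion, the baseline c-ACT, CASI and PAQLQ fall after the first injection, so the score comparisons mix on-drug with pre-drug baselines

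*Protocol article*

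**What the plan says.** Section 4.1 admits two kinds of patient: "Patient currently under treatment or who initiates treatment with mepolizumab at the inclusion visit".

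Section 4.4, Table 3, has one baseline column for both. Its first header adds, to the 12 months before initiation, the time "since mepolizumab initiation to inclusion visit in patients already under treatment", together with current data. When the header is repeated lower down, it reads "Retrospective data (12 months prior inclusion) and current data".

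The scores are scheduled as follows.

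- **c-ACT:** Table 2 says "It will be completed at baseline and follow-up visits"; Table 3 marks baseline and all follow-up visits.
- **CASI:** Table 1 has "Degree of asthma severity (CASI score at baseline, 12- and 24 months", and Table 3 agrees.
- **PAQLQ:** Table 2 has it filled in during visits; Table 3 marks baseline, 12 and 24 months only.

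Section 3.2 then plans to "Compare the level of asthma control at baseline and the 12- and 24-month post-exposure periods", and likewise for CASI. It also plans to describe the quality of life "of patients treated with mepolizumab at the pre-exposure and post-exposure periods".

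The notes under Table 3 define the pre-exposure period as the 12 months before initiation. The post-exposure period runs up to 24 months from initiation and may be partly retrospective.

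**The concern.** A comparison of control or severity between baseline and 12 or 24 months of exposure will be read as before versus after drug. That reading is right for a child who starts at inclusion and completes the questionnaire before the first injection. For a child already treated, the inclusion visit lies inside the post-exposure period, so the baseline score may already contain part or all of the drug's effect.

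The pooled change then depends on the recruitment mix and on time on drug at inclusion, as well as on the drug itself. A small mean change in c-ACT or CASI could reflect a small effect or many existing users, and the pooled figure alone would not show which. For PAQLQ the difficulty is different: the objective needs a pre-exposure value, and the schedule provides none for existing users.

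**Working it through.** **Step 1. Can baseline be on drug?** Yes. Section 4.1 admits existing users, and the first Table 3 header describes an interval between initiation and the inclusion visit for them. Table 3 also asks for satisfaction with treatment at baseline only from children already treated, which makes sense only if that visit is on drug.

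**Step 2. Which outcomes use that visit as their anchor?**

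| Outcome | Anchor in the article | Affected? |
|---|---|---|
| Exacerbations (primary, and secondary rates) | 12 months before initiation | No |
| Maintenance OCS dose | Index date, i.e. mepolizumab start | No |
| c-ACT, CASI | Baseline, not defined further | Yes, for existing users |
| PAQLQ | Objective: pre-exposure; schedule: baseline visit | Yes, for existing users |
| FEV1, FVC | 12 months before to 24 months after initiation (Section 3.3) | Not part of this point |
| Eosinophils, FeNO | Change during the treatment period (Section 3.3) | Not part of this point |

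The article uses an initiation-based anchor where it wants one, but not for c-ACT and CASI. Elsewhere the two dates are blurred: the fourth inclusion criterion in Section 4.1 writes enrolment date and index date as alternatives for one date, and the two Table 3 headers end the look-back at different dates.

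**Step 3. Size.** The article states no figure on this point to reproduce; its one sample-size calculation concerns the exacerbation rate. Let D be the true mean pre-to-post change, p the share already treated at inclusion, and f the fraction of D already present at inclusion. Assume the same D in both groups and no charted pre-drug score among existing users.

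- New starters show a change of D.
- Existing users show (1 − f)·D.
- Pooled mean: (1 − p)·D + p·(1 − f)·D = (1 − p·f)·D.

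The article gives neither p nor f. Under assumed values:

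| p | f | Observed / true | Lost |
|---|---|---|---|
| 0.25 | 0.5 | 1 − 0.125 = 0.875 | 12.5% |
| 0.25 | 1 | 1 − 0.25 = 0.75 | 25% |
| 0.5 | 0.6 | 1 − 0.30 = 0.70 | 30% |
| 0.5 | 1 | 1 − 0.50 = 0.50 | 50% |
| 0.75 | 1 | 1 − 0.75 = 0.25 | 75% |

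**Step 4. Limits of the formula.** If a share c of existing users has a charted pre-drug score and it is used, the factor becomes 1 − p·(1 − c)·f, which is closer to 1. The formula also does not cover a child included more than 12 months after starting, whose inclusion-visit score comes later than the 12-month point with which it would be compared.

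**The case against.** The strongest reply is that the baseline column of Table 3 takes retrospective chart data as well as current data, and that c-ACT and CASI are marked in it. A score charted before the first injection could therefore serve as baseline. This stands in part: it is possible for some children, and it is why the attenuation is conditional. But no text says to use such a value, and Table 2 describes questionnaires completed at the visit. The route is least plausible for PAQLQ.

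Second, quality of life is only to be described, so no planned PAQLQ contrast is diluted. That is right. What remains for PAQLQ is the absence of a scheduled pre-exposure value for existing users.

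Third, this is a condensed article, and the full protocol or the analysis plan may define baseline. It may; the design figure under the Baseline data heading was also not available for this check. The point nevertheless rests on what the article does state: its eligibility rule, its visit schedule and its objectives do not fit together. An analysis plan also cannot supply a PAQLQ that was never collected before treatment.

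Fourth, the treatment start date is collected, so new starters can be separated from existing users. This is true, and it makes the problem repairable. A reader might infer that a small score change would be beyond interpretation altogether; the documents do not support that.

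**Conclusion.** The point holds for c-ACT and CASI as a mixture of on-drug and pre-drug baselines in a planned comparison, and for PAQLQ as a missing scheduled pre-exposure value in existing users. It concerns secondary objectives only.

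The size is unknown. A loss of 30% to 50% at p = 0.5 and f from 0.6 to 1 is illustration, and it requires that the drug improves the scores and that existing users have no charted pre-drug score.

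Three stronger readings should be resisted.

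- **Every existing user dilutes the result by a known amount.** Neither p nor f is stated, and some children may have chart values.
- **Lung function, eosinophils and FeNO share the fault.** Section 3.3 gives lung function a window starting before initiation, and describes eosinophils and FeNO only during treatment.
- **The main result is compromised.** The primary exacerbation comparison is anchored at initiation and is unaffected, as are children who start at inclusion.

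**What to change.** 1. Define baseline for c-ACT, CASI and PAQLQ as the last value on or before the first injection, within the 12-month pre-exposure window. For new starters this is the inclusion-visit value, taken before the injection.
2. Run the pre/post comparisons of c-ACT and CASI, and describe pre-exposure quality of life, only in children who have such a value. State how many do.
3. Report existing users' inclusion-visit scores separately, as on-treatment values by months since first injection.
4. Reconcile the two baseline headers in Table 3, so that it is clear whether the look-back ends at initiation or at inclusion.

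This needs no additional visits: the start date is already collected, and the index date is already the anchor for OCS dose. The cost is fewer children, and so less precision, in the score-change analyses. PAQLQ is likely to lose most, since a charted pre-drug value is least likely there.

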### 3.3 Other objectives

Where data is available, additional objectives will be addressed:

Describe patient & parental satisfaction with mepolizumab treatment.Describe health care professional satisfaction with mepolizumab treatment in general and per type of treatment (home vs hospital).Describe lung function using the change in FEV_1_ and FVC (measured in L and using GLI reference values) during the observational period (12 months pre and 24 months post mepolizumab initiation).Describe the change in peripheral blood eosinophils during the post mepolizumab treatment period.Describe the change in FeNO during the post treatment period.Characterise and compare patterns of school absenteeism and parental work status, (productivity/absenteeism) at baseline and the 12- and 24-month post-exposure periods.To assess the clinical profile of the subgroup of paediatric patients who start treatment with mepolizumab, after omalizumab discontinuation.To assess changes in growth profile of the patients under treatment with mepolizumab at baseline and the 12 and 24-month post-exposure periods.

